## Abstract

**Background and objective:**

Musculoskeletal disorders (MSDs) including upper crossed syndrome (UCS) are considered as the leading cause of work-related issues worldwide among office workers. Therefore, the present study aims to evaluate the effect of workplace-based versus online-supervised home-based corrective exercises among office workers with UCS.

**Methods and design:**

To this end, 45 subjects within the age range of 30–45 years are randomly assigned to three groups in the present parallel-group, randomized control trial using a pretest-posttest design. These groups include the subjects who receive online-supervised exercise and workplace exercise containing three sessions of intervention for 8 weeks and the control group receives no intervention while performing routine activities. The primary outcome variables are neck-shoulder pain (NSP) and consequent sick leave due to NSP, followed by alignment, workability, and the surface electromyography of upper, middle, and lower trapezius (UT, MT, and LT), sternocleidomastoid (SCM), and serratus anterior (SA) as the secondary variables.

**Discussion:**

The present study seeks to assess the effect of workplace versus online-supervised corrective exercise interventions among 45 office workers suffering from UCS. It is expected to improve and reduce the related symptoms including postural malalignment and imbalance muscles after 8 weeks of corrective exercises. If effective, the findings may lead to adherence and work performance among the office workers, and individuals subjected to UCS can use the benefits of an online-supervised intervention. In addition, the findings may be useful in different workplaces as the evidence for employers to benefit from the reduction in the related costs and side effects of work-related neck/shoulder disorders including work disability, productivity loss, time expense, social insurance, work absenteeism, and treatment costs. Finally, clinicians and corrective exercise therapists can consider it as a clinical based-evidence intervention for their further actions.

**Trial registration:**

Iranian Registry of Clinical Trials IRCT20200729048249N1. Registered on 5 October 2020 (https://en.irct.ir/user/trial/49992/view)

## Background

Nowadays, sedentary work is considered predominant in various parts of the world due to the rapid development of technology and the new nature of work. The workers are exposed to prolonged static posture and repetitive upper limb movements [1, 2] and spend long periods in front of a computer or at a desk in a dorsiflexed position with rounded shoulders [3]. According to Page [4, 5], these prolonged postures may under-activate some muscles while over-activating other muscles leading to joint dysfunction known as “upper crossed syndrome” (UCS). In addition, specific postural changes due to the UCS may decrease glenohumeral stability causing elevated shoulders and scapulae winging. Accordingly, the levator scapula and upper trapezius require increasing activation in order to maintain glenohumeral centration to compensate for the loss of this stability [4–7]. All these alterations may be associated with work-related neck/shoulder disorders (WNSDs) although the casualty of the association between computer use and pain is unknown [8].

As one of the main concerns of public health, WNSDs may be related to pain and impaired physical functions causing musculoskeletal complaints and affecting work performance among the office workers [9]. Further, WNSDs with annual prevalence rates of 27–48% influence the musculoskeletal system leading to numerous work-related disorders [10, 11]. Regardless of the actual cause of pain, musculoskeletal pain in the neck and shoulders increase the risk of long-term sickness absence in white-collar workers [12]. The prevalence of this type of pain was reported relatively high in the neck and shoulders (45.8 and 40.1%, respectively) in Iran [13]. Thus, different employees are at an increased risk of sickness absence. Regarding the major role of WNSDs in both employees and employers, as the most common reasons for work disability, sick leaves, and early retirement, it is considered as one of the most significant current discussions due to the cost accompanying treatment, production loss, and work absenteeism [14–16]. Thus, it has become one of the most serious challenges in occupational health for reducing the financial impacts of health-related productivity and labor costs among office workers as a worthwhile business consideration [17].

Neck or shoulder pain symptoms appear to intensify since office workers with UCS generally sit with curved postures, take prolonged constant muscle activity, and perform repetitive job tasks [18, 19]. Pain is considered as the strongest stimulus to central motor programming, which can alter electromyography (EMG) patterns in functional tasks since it has an inhibitory effect on muscle activation [20]. Some clinical studies confirmed that the tenderness of muscles is considered the most common type of neck or shoulder pain in office workers [19, 21, 22].

Due to the relationship between neck or shoulder pain and muscle tenderness, some studies reported that computer workers with neck and shoulder pain might have trapezius myalgia, tension neck syndrome, and cervicalgia [22, 23]. Thus, the majority of the office workers with frequent pain in shoulder and neck experienced tenderness of the upper trapezius muscle [23]. Further, Pietropaoli et al. reported higher EMG activity by more muscle tenderness scores when a general correlation was observed between muscle tenderness and EMG values [24].

Thus, individuals with insidious-onset cervical pain demonstrate poor postural stability more and significantly increased EMG levels in the SCM activity, respectively [25, 26].

Furthermore, due to the affected regions of painful UCS and alteration in muscle activation around the scapula and neck, EMG can be used as a reliable tool to validate the assessment of LT, MT, and SA activity decrease as well as UT activity increase [27–29].

Among office workers, postural changes and movement patterns in the scapula refer to the UCS including postural malalignments and altered muscle activity associated with workability and sickness absence [30]. Such conditions may play an important role in the development of neck and shoulder pain, which can be measured with electromyography as far as physiological measurement is concerned [31]. Meanwhile, balancing and restoring muscle activity by maintaining the alignment (upright body position) can reduce chronic neck pain and induce a more relaxed muscle activity pattern during work [32]. Due to the study population and WRMSDs impacts containing workability and sickness absence, it is evident the importance of managing UCS symptoms along with monitoring muscle activity to decrease the incidence of subsequent impairments [33].

Then, knowledge is highly required regarding effective interventions for relieving WMSD symptoms and preventing the related consequences such as pain, work disability, and sickness absence [34]. In this regard, some studies reported statistically significant positive effects for improving office workers’ workability by increasing physical activities [35]. Additionally, the results of some studies demonstrated that exercise has positive effects on health-related productivity loss and sickness absenteeism among office workers with neck pain in the longer term [36]. In addition, Seeberg et al. found a relationship between forward head posture (FHP) improvement and musculoskeletal pain after therapeutic exercises [34]. Further, the results of some studies indicated that exercises specific to the involved muscles restored malalignment and increased the ability to keep an upright cervical posture during work, as well as improved pain, disability, and the quality of life among office workers [37, 38]. On the other hand, considering that different mechanisms may contribute to abnormal scapular movements, pain, abnormal thoracic posture, and imbalance muscle strength or activation [39], an exercise program can improve neck pain displaying positive and significant alterations in the forward head and protracted shoulder posture, disability, and the timing of superficial neck muscle activation [40, 41]. Finally, some positive effects of exercise interventions are presented for improving postural malalignments based on the majority of studies. However, both the neural and muscular components should be considered to accomplish the best performance [42–45].

Although previous studies have revealed the hopeful results of exercise interventions among different occupational groups, the question that remains is whether such interventions should be implemented under supervision or in the workplace [34, 46]. The performance of worksite exercises in a group may be more motivating for some employees regarding increasing adherence although various barriers exist in this respect during working hours, which may be costly for employers regarding spending time and facilities [46]. Furthermore, although previous literature has demonstrated the positive efficacy of both supervised and unsupervised exercise programs, contradictory results are present about whether supervised or unsupervised exercise is more effective [47–49]. Several studies have simultaneously addressed all the involving factors related to UCS by applying exercise therapy. However, scarce research has focused on some separate areas of the upper body including the neck or shoulder among office workers [19, 40, 43, 50–53]. According to Hall et al. [54], the world is currently experiencing an extraordinary, life-altering challenge due to social distancing and home quarantine recommended by the World Health Organization to minimize the speed of the coronavirus disease (COVID-19). Outdoor physical activities have been postponed in different cases [55, 56] since it is difficult to precisely predict when the COVID-19 pandemic diminishes and communities can return to normal function [57]. Accordingly, online-guided physical activities at home may be a way forward. Thus, studying the effect of workplace versus online-supervised exercises among office workers suffering from WMSDs including UCS is relevant.

### Objectives

Given the explanations mentioned earlier, the present study seeks to evaluate the effect of workplace-based versus online-supervised home-based corrective exercises containing NSP and sick leave due to NSP as the primary objectives.

The secondary objectives include workability, alignment (i.e., neck, shoulder, and thoracic spine angles), and assessing the surface EMG of designated muscles including UT, MT, LT, SCM, and SA among office workers with UCS.

## Method

### Study design

A parallel-group randomized control trial with a pretest-posttest design is used for the present study. Additionally, the selected subjects are randomly assigned to three groups including two interventions (i.e., online-supervised exercise and workplace exercise receiving 8 weeks of intervention) and a control group with no intervention performing routine activities. In addition, baseline assessments are organized at the Sports Science and Health Laboratory at Shahid Beheshti University, Tehran, Iran, and are repeated after 8 weeks of intervention. The procedure and flow diagram are shown in Table 1 and Fig. 1, respectively. The procedure is followed according to the SPIRIT^1^ guidelines to ensure the apparent and standardized reporting of the trial.

**Table 1 Tab1:**
[figure not shown]
Procedure of the study

**Fig. 1 Fig1:**
[figure not shown]
Study flowchart

### Ethical considerations

Before commencing the study, the procedure including assessments is explained to the subjects, and they are requested to complete and sign an informed consent form. Ethical clearance No. IR.SBU.REC.1399.036 dated 20 June 2020 was issued by the Ethics Committee on the Research at Shahid Beheshti University, Tehran, Iran. Further, IRCT No. IRCT20200729048249N1 dated 5 October 2020 was approved by the Iranian Registry of Clinical Trials (https://en.irct.ir/user/trial/49992/view). Furthermore, deviations from the present protocol are clearly described in the main article with the results of the trial.

### Subjects and eligibility criteria

The corrective exercise specialist (Ph.D.) primarily screens the subjects recruited through invitation letters from private and public organizations in Tehran, Iran, for three main UCS features. Since the presence of scapular dyskinesia may indicate the lack of neuromuscular control, including muscle activation and timing thus, the related tests are performed to evaluate the position and rhythm of the scapula, which plays a significant role in facilitating the upper extremity function among office workers [58–60]. Further, due to any postural alteration influencing the muscle activity, muscle length and muscle strength tests are implemented for UT and pectoral muscles and MT, LT, and deep cervical flexor, respectively [61].

Inclusion criteria for the trial must comply with office workers between 30 and 45 years using a computer or lab-tops most commonly during the working day (about 30 h per week) with at least 5 years of experience [17, 62]. Having alignment alteration includes forward head (≥ 45°), round shoulder (≥ 52°), and round back (≥ 42°) according to previous studies [63, 64]. Marking pain intensity score visual analog scale (VAS) ≥3 in neck and shoulder [17, 58, 65].

Concerning exclusion criteria, those are ineligible if pregnant during the study process, having surgery on the upper extremities during the past year, unable to perform exercise due to any medical conditions, and being in weight out of the normal range (18 ≥ BMI ≥ 25).

Drop out criteria are considered if the subjects attend no post-tests, lose three sequential intervention sessions, and any factors that may affect the study results.

However, the subjects are allowed to discontinue the study at any stage [66]. At the first encounter at baseline, the researchers are asked for permission to contact them in the case of study discontinuation. Accordingly, performing an accurate intention-to-treat analysis of the primary result is possible.

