### Intervention

As illustrated in Figs. 2 and 3, an 8-week corrective exercises protocol is taken by two intervention groups considering the UCS features such as alignment, muscle activity, and movement pattern simultaneously. The exercise program is performed three days per week to achieve the best results. Each session lasts nearly 50 min, initiating by 5–7 min of warm-ups and finishing by cool-down, respectively [59]. In addition, the exercises are initiated by three repetitions holding for 10 s using the Borg scale [68] and progress to six repetitions, holding for 25 s based on overload principles and individual characteristics [59, 61]. If reporting pain during the exercise performance, the subjects can discontinue and rest until pain relief, while moderating the exercises accordingly. A qualified corrective exercise instructor supervises the exercise programs of both intervention groups. The online-supervised group includes up to four subjects. Each session is remotely performed and supervised three times a week for 8 weeks in their home environment using real-time desktop videoconferencing software (https://meet.jit.si/) via a laptop computer. Accordingly, subjects can have contact and talk with both the instructor and the other subjects [62]. The workplace group performs all sessions in the worksite without daily face-to-face supervision, although supervision is conducted using diary and telephone interviews. Further, each participant in this group is provided with a detailed written exercise and pictorial descriptions to enhance exercise performance. However, the corrective exercise expert is present once a week during the exercise sessions to provide input and evaluate the progress and ensure that all subjects are exercising safely and correctly [49]. It is noteworthy that the corrective exercises protocol is expected to prevent the undesired lack of scapula stabilization on the thorax diminish neck and shoulder pain. Individuals with shoulder pain have excessive upper trapezius activation and decreased and/or delayed activation of the LT, MT, and SA [66]. Thus, exercises specifically targeting the trapezius and SA muscles are commonly incorporated into rehabilitation programs to optimize the scapular position and motion [69]. Recent studies indicated that the specific training of the neck muscles, such as strengthening deep cervical flexor muscles, could reduce neck pain and improve SCM endurance, which is effective in correcting head and shoulder postures [68, 70]. Therefore, these exercises are recommended to improve the function of muscles in the neck, shoulder, and thoracic for several painful conditions due to their reduced or altered activation. At the follow-up, subjects are asked whether they have experienced any injuries or other adverse events during the training sessions.

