### Outcome measures

Before randomization and at baseline, all assessments are performed and repeated after the intervention. NSP and sick leave due to pain are considered as the primary outcome variables, followed by the alignment, workability, and electromyography (EMG) activities of the selected muscles as the secondary variables. In the first part of the questionnaire, the subjects are asked to insert their demographic and social status including gender, age, weight, and height (body mass index = kg/m^2^), work hour/week, years of experience, education level, and marital status [71].

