#### Workability and sick leave due to pain

Workability is self-assessed using the related questionnaires by a single validated item from the workability index [73, 74]. The subjects respond to one question as to how they rate their current workability according to their capabilities to meet the mental and physical demands of their job, which can still perform in two years. The response scores range from 0 to 10, indicating inability to work and workability with a cut-off point score of ≤7 implying poor workability, respectively [75]. In addition, sick leave due to pain is evaluated using a single item from the validated Outcome Evaluation Questionnaire to obtain data on the number of absence days from work due to pain in muscles or joints within the past month, and response categories ranged from 0 to 31 days [76]. Based on a recent meta-analysis, self-reported sick leave demonstrates good reliability and validity against the records [77].

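### The three-lost-sessions drop-out rule works differently by arm, is linked to the sick-leave primary outcome, and is not reconciled with the intention-to-treat statement

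*Protocol article*

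**What the plan says.** **The rule.** Protocol article, Subjects and eligibility criteria: "Drop out criteria are considered if the subjects attend no post-tests, lose three sequential intervention sessions". The sentence closes with a catch-all for anything else that might influence the results. It makes no exception for sick leave and no provision for moving or making up a session. The next paragraph lets subjects leave at any stage, has permission for later contact sought at baseline, and concludes that an intention-to-treat analysis of the primary result can be carried out. It does not say whether someone classed as a drop-out for lost sessions is post-tested or analysed, and it does not mention the secondary outcomes.

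**The arms.** Intervention, both exercise arms: "The exercise program is performed three days per week to achieve the best results". Workplace arm: "The workplace group performs all sessions in the worksite without daily face-to-face supervision". Online arm: "Each session is remotely performed and supervised three times a week for 8 weeks in their home environment". Third arm, in Study design: "a control group with no intervention performing routine activities".

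**The outcome.** Outcome measures: "NSP and sick leave due to pain are considered as the primary outcome variables". Sick leave is a single self-reported item, "the number of absence days from work due to pain in muscles or joints within the past month", answered from 0 to 31 days.

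**Analysis and size.** Statistical method and analysis compares the groups by ANCOVA on the post-test value and names no analysis set. Sample size calculates 11 per group and raises this to 15 to cover losses.

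**The concern.** The rule acts after randomisation, and how easily a person meets it depends on the assigned arm. For a workplace participant, being off work means being away from the only place where sessions are held. For an online participant, being off work leaves the home session available. For a control there is nothing to miss.

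The event behind the trigger in the workplace arm, a spell away from work, overlaps with what one of the two primary outcomes counts. If meeting the rule takes a person out of the post-test or the analysis, the workplace arm loses some of its long leave spells while control keeps all of its own and the online arm keeps most. Workplace sick leave would then look lower than it is, against control and, to a lesser degree, against online. Pain would probably move in the same direction, since people with long pain-related leave are likely to have worse pain.

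**Working it through.** **Plan's own figure.** Reading the stated effect size of 0.66 as Cohen's f with two groups, alpha 0.05 and 80% power, a fixed-effects ANOVA needs 11 per group (power 0.837), which matches the article. With three groups it would be 9. Read as a standardised mean difference, 0.66 would need 37 per group two-sided. The allowance is 15 − 11 = 4 of 15, or 26.7%. The point here does not rest on the choice of 11.

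**Step 1: how much absence meets the rule in the workplace arm.** Inputs are three sessions a week at the worksite, a trigger of three in a row, and no make-up sessions (an assumption, since the article is silent). Take a 5-day working week, all 10 ways of placing three sessions in it, and all 5 start days of a run of consecutive working days off, giving 10 × 5 = 50 combinations:

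- 3 days off: 5 of 50 cover three sessions in a row (10%).
- 4 days off: 20 of 50 (40%).
- 5 days off: 50 of 50 (100%).

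With a 6-day working week, 5 days off covers three in a row in 50% of combinations and 6 days in 100%. So a full working week off always meets the rule.

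**Step 2: the other arms.** Control has no sessions, so the probability is zero. In the online arm the rule applies, but only home sessions that are actually missed count towards it.

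**Step 3: effect on mean sick leave if those who meet the rule are left out.** None of these inputs is in the documents. Let q be the share of workplace participants with one 5-day spell in the 8 weeks, with half of the spells inside the past-month window (roughly the last four of eight weeks). Let background leave be 0 to 2 isolated days with mean 0.5, and assume no true effect.

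- Mean with everyone included: 0.5 + 5 × q × 0.5 = 0.5 + 2.5q.
- Mean after removal: 0.5.
- False reduction: 2.5q. The background cancels.

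| q | Mean, all | After removal | False reduction (days) |
|---|---|---|---|
| 5% | 0.625 | 0.50 | 0.13 |
| 10% | 0.75 | 0.50 | 0.25 |
| 20% | 1.00 | 0.50 | 0.50 |

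Longer spells enlarge this. If everyone is followed and analysed as randomised, it is zero.

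**Step 4: numbers remaining in the workplace arm.** Expected losses are 15q. The chance that fewer than 11 remain is P(Bin(15, q) ≥ 5).

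| q | Expected losses | P(fewer than 11 remain) |
|---|---|---|
| 5% | 0.75 | 0.1% |
| 10% | 1.5 | 1.3% |
| 20% | 3.0 | 16.4% |
| 30% | 4.5 | 48.5% |

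**Step 5: the rule as a measure of exposure.** Three sessions a week for 8 weeks make 24. Someone who misses one week attends 24 − 3 = 21 (88%) and meets the rule. Someone who comes only to every third session attends 24 / 3 = 8 (33%), never misses more than two in a row, and does not.

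**The case against.** The strongest reply is that the article nowhere says that a person who meets the rule is barred from the post-test or excluded from analysis. It plans for contact after discontinuation and mentions intention-to-treat analysis. Both primary outcomes are questionnaire items that need no laboratory visit. Analysis sets are often left to a fuller document that is not shown. On that reading the bias is zero. This stands as a limit: bias is conditional, not demonstrated. It does not settle the matter, because the article lists lost sessions beside missing the post-test and a catch-all for factors affecting results, enlarges the sample to cover lost subjects, and says only that intention-to-treat analysis can be done, for the primary result alone.

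A reader might infer more than the text supports:

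- *That a week of leave automatically removes a workplace participant.* This needs both no make-up sessions and exclusion after the trigger. The article states neither.
- *That the online arm is unaffected.* The rule applies there too, and someone off work with neck-shoulder pain, or travelling, may miss home sessions. Only control is fully exempt.
- *That the primary outcome itself removes people.* Trigger and outcome overlap but differ. Only pain-related days in the past month are counted, so a spell in about weeks 1 to 4 meets the rule without being counted at post-test. Leave for another cause meets it without ever being outcome leave, and scattered pain days may count without meeting it.
- *That the bias is very large.* With 10% having a 10-day spell wholly inside the window, 0.5 day in the rest and full exclusion, the means are 0.1 × 10 + 0.9 × 0.5 = 1.45 against 0.50, a false reduction of 0.95 day (66%). Every one of these inputs is assumed, and they are unfavourable ones.

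The 21-versus-8 contrast in attendance is correct but hypothetical. It supports reporting adherence as a count and shows nothing about bias.

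**Conclusion.** The point holds in conditional form. As written, the lost-session criterion depends on arm and is linked to a primary outcome. With no make-up sessions, a full working week off work meets it in the workplace arm, whereas control can never meet it and online participants do not meet it through absence from work alone. The article does not reconcile the criterion with its intention-to-treat remark.

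If those who meet it are left out of the post-test or analysis, workplace sick leave, and probably pain, is biased in favour of the workplace arm. The illustrative size is 0.13 to 0.50 day, resting on 5-day spells, half of them inside the window, 5% to 20% of people affected, and full exclusion. None of these comes from the documents. The effect on numbers is slight at 5% to 10% affected and becomes material at 20% or more.

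**What to change.** In Subjects and eligibility criteria, state that missing sessions does not end study follow-up; that every randomised subject is invited to the post-test and analysed in the assigned arm, for primary and secondary outcomes alike; and that lost sessions are reported only as adherence, as sessions completed out of 24 with the reasons for those missed, including sick leave. This concerns follow-up and analysis only and leaves the handling of the exercise programme as it is.

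The cost is one or two sentences and a few extra post-tests. Keeping poor attenders in the analysis slightly dilutes the estimated exercise effect.

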### Statistical method and analysis

Data are analyzed using IBM SPSS statistics software, version 24 for Windows, and descriptive statistics are applied to describe the variables considering sig. ≤0.05. Further, data normality is reported based on the Shapiro-Wilk test.

A 3 (group) × 2 (time) mixed-model repeated-measures ANOVA is used to compare all values from the pre-test to each point of the time within each group. Furthermore, the mixed-model repeated-measures ANOVA is applied to analyze within-group changes. Additionally, Bonferroni’s post hoc test for indicating the significance is utilized for any significant difference, and one-way ANCOVA is employed to compare the groups in the post-test with each pre-test value as a covariate. In addition, the effect size is calculated for the magnitude of the difference using the partial *η*2 method as small (0.01 ≤ *η*2 < 0.06), medium (0.06 ≤ *η*2 < 0.14), or large (*η*2 ≥ 0.14). It should be noted that interim analyses were not planned in the present study.

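### Two drop-out criteria act after randomisation, one of them only in the exercise arms, and neither is reconciled with the intention-to-treat analysis that the protocol calls possible

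*Protocol article*

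**What the plan says.** All the wording at issue is in the protocol article.

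- **Subjects and eligibility criteria, drop-out rule.** The list opens with "Drop out criteria are considered if the subjects attend no post-tests" and continues with "lose three sequential intervention sessions, and any factors that may affect the study results". It does not say what follows for the analysis set.
- **Same section, next paragraph.** Participants may leave at any stage, and at baseline the researchers seek "permission to contact them in the case of study discontinuation". The paragraph ends: "Accordingly, performing an accurate intention-to-treat analysis of the primary result is possible".
- **Study design.** The third arm is "a control group with no intervention performing routine activities".
- **Intervention.** "The exercise program is performed three days per week", for 8 weeks. Online sessions are supervised live. Workplace sessions are followed by diary and telephone, with an expert present once a week.
- **Statistical method and analysis.** The groups are compared by a 3 × 2 repeated-measures ANOVA and by an ANCOVA to "compare the groups in the post-test with each pre-test value as a covariate". No analysis set is named.

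**The concern.** Having no post-test is a fact about the data. The other two criteria are decisions about people who have already been randomised. One of them cannot be met in the control arm, since there is nothing there to miss. The other has no limits: almost anything that happens to a participant might affect the results. If either criterion decides who is followed up or analysed, the arms are no longer the groups that randomisation formed.

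Both kinds of contrast are exposed. Against control, selection operates on one side only. Between workplace and online exercise, the arms may differ in how often sessions are missed and also in how reliably a missed session is noticed, because one arm is watched live and the other is mostly followed by diary and telephone.

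**Working it through.** **1. The plan's own figures.** The Sample size section gives 11 per group (alpha 0.05, power 80%, effect size 0.66), raised to 15 to cover losses. Eleven per group is reproduced by a two-group F test with 0.66 read as Cohen's f (smallest total 21). It is also reproduced by a two-group, two-time interaction with f = 0.33 (d = 0.66) and an assumed correlation of 0.5 (again 21). The point here does not depend on which was used. The loss allowance is 1 − 11/15 = 4/15 = 26.7% per arm.

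**2. How easily the missed-session criterion is met.** Sessions planned: 3 × 8 = 24. Three in a row is 3/24 = 12.5%, or one week. A participant who attends 21 of 24 sessions (87.5%) can therefore meet it.

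**3. Who can meet each criterion.**

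| Criterion | Online | Workplace | Control |
|---|---|---|---|
| No post-test | yes | yes | yes |
| Three missed sessions in a row | yes | yes | cannot occur |
| Open-ended clause | yes | yes | yes |

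**4. Pain: size of the bias if those people are removed.** Let p be the fraction of an exercise arm removed in excess of control, and D the amount by which those removed would have scored worse on the VAS than those kept. The mean of those kept is better than the full-arm mean by

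bias = p × D.

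The documents give neither quantity. I assume p from 0 to 4/15 (the whole loss allowance, falling in the exercise arm only) and D from 0.5 to 1.5 points:

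| Excess removed | D = 0.5 | D = 1.0 | D = 1.5 |
|---|---|---|---|
| 0 of 15 | 0 | 0 | 0 |
| 1 of 15 | 0.03 | 0.07 | 0.10 |
| 2 of 15 | 0.07 | 0.13 | 0.20 |
| 3 of 15 | 0.10 | 0.20 | 0.30 |
| 4 of 15 | 0.13 | 0.27 | 0.40 |

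If D = 0 the bias is zero. If D is negative (those removed were doing better), the same sizes apply against exercise.

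**5. Pain: check by simulation with no true effect.** The least adherent are removed from the two exercise arms only. The assumed correlation between poor adherence and worse final pain is r. Bias is in outcome SDs, and minus favours exercise:

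| Removed | r = −0.3 | r = 0 | r = 0.3 | r = 0.5 |
|---|---|---|---|---|
| 10% | +0.06 | 0 | −0.06 | −0.10 |
| 20% | +0.11 | 0 | −0.11 | −0.18 |
| 26.7% | +0.13 | 0 | −0.13 | −0.22 |

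With 11/11/15 analysed, pooled exercise against control is falsely significant in favour of exercise (nominal 2.5%) in 2.6%, 5.7% and 9.8% of trials at r = 0, 0.3 and 0.5. The three-group F test (nominal 5%) rejects in 5.0%, 6.3% and 8.6%.

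**6. Sick leave.** This primary outcome counts days off work with pain in the past month (Workability and sick leave due to pain). Workplace sessions all take place at the worksite. A participant in that arm who is off work with pain for a week would ordinarily miss three sessions in a row and so meet the criterion. If that week falls in the month before the post-test, it is also the outcome being counted. A control with the same absence stays in. Illustration: in an arm of 15 with one person absent 5 days and the rest at zero, the mean is 5/15 = 0.33 days. With that person removed it is 0/14 = 0.

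**The case against.** The strongest reply is that the section never says drop-outs are excluded from analysis. It provides for contact after discontinuation and draws from that the feasibility of intention-to-treat. On this reading, people drop out of the programme but are still followed up and analysed as randomised. That reading is possible, so outright contradiction is not proven. It is not the natural one, however. Voluntary discontinuation is dealt with separately afterwards. Missed sessions are listed beside having no post-test, which does remove a person from the post-test ANCOVA. A clause about protecting the results has little purpose unless someone is taken out. Even on the kinder reading, the section leaves unclear who enters the primary analysis.

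Some stronger readings are tempting, but the documents do not support them:

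- *That intention-to-treat is promised.* It is only called possible, and only for the primary result.
- *That the pain comparison is biased towards exercise.* Nothing links missed sessions to pain outcome. The Background mentions barriers to exercise during working hours, which need not relate to pain at all. The open-ended clause has no fixed direction.
- *That unblinded staff apply the open-ended clause.* The text does not say who applies it. The Randomization section has the investigator assign participants and says the process is not independent of the investigators, so it could be applied with knowledge of the group, but no more than that.
- *That the bias is about a quarter of the planning effect.* With an assumed SD of 1.5, 0.27/1.5 = 0.18 SD, which is 27% of 0.66 if that is Cohen's d but about 13% if it is f (d = 1.32). The protocol does not say which. The figure also places all loss in the exercise arm, whereas the allowance covers every arm. Equal loss with equal deficits gives no bias.
- *That the handling of missing post-tests is a defect.* An article commonly leaves this to a full protocol or analysis plan, and neither is shown.

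**Conclusion.** The concern holds in a limited form. The protocol fixes two post-randomisation drop-out criteria, one confined by design to the exercise arms and one without bounds, and does not reconcile them with its intention-to-treat sentence. If people who meet them leave the trial or the analysis, the comparison is open to selection that depends on arm.

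For pain, size and direction depend on unknown quantities. Under the assumed ranges for loss and deficit the bias is 0 to 0.40 VAS points, favouring exercise if poor responders miss sessions and reversing if improvers do. The case is firmer for sick leave in the workplace arm, where the outcome itself can trigger the criterion and its removal would favour exercise. How often that would happen cannot be judged from the documents.

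**What to change.** Reconcile the section as follows:

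1. Record missed sessions, including three in a row, as a measure of adherence rather than as a drop-out criterion.
2. Delete the open-ended clause about factors affecting the results.
3. Seek the week-8 assessment from every randomised participant, using the contact permission already requested. Where a visit is not possible, obtain at least the pain and sick-leave questionnaire.
4. State that the primary outcomes are analysed in the assigned group, and label any adherers-only analysis as a sensitivity analysis.

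This concerns follow-up and analysis only, not whether or when someone stops exercising. The cost is a change of wording, taken through the amendment route that the Randomization section describes, and a few extra follow-up contacts. The estimated effect may be somewhat diluted, because participants who exercised little stay in their assigned arm.
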